**Research Question 2b**: Do measures of user preferences identified during a brief test-drive session with an *actual* AFO predict user preferences after the same *actual* AFO is worn longer-term in the community environment?

**Hypothesis 2b**: Initial preference scores for each *actual* AFO be strongly correlated with preference at follow-up.

**Research Question 2c**: Do measures of user preferences identified during a brief test-drive session correlate with performance measures and self-reported measures of mobility after the same *actual* AFO is worn longer-term in the community environment?

**Hypothesis 2c**: Initial *emulated* preference scores be strongly correlated with performance-based and self-reported mobility measures at follow-up.

**Research Question 2d**: Do measures of user preferences identified during a trial with the *actual* AFO correlate with performance measures and self-reported measures of mobility after the same AFO is worn longer-term in the community environment?

**Hypothesis 2d**: Initial *a*ctual preference scores be strongly correlated with performance-based and self-reported mobility measures at follow-up.

**Exploratory Aim:** Allow the user to self-tune AFO emulator stiffness settings while walking (***patient-optimized***) and compare function, mobility, preference to the clinically prescribed AFO (***clinician-optimized***). This aim will determine if an AFO test drive strategy can be used to better optimize user satisfaction and patient reported outcomes relative to the current standard of care.

**Research Question 3a**: How does preference differ between the patient-optimized setting on the AFO emulator and in the clinically-prescribed *actual* AFO?

**Hypothesis 3a**: Preference scores for the user-optimized setting on the emulator will be greater than those in the clinically prescribed AFO.

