• **Pain**. Ankle/foot pain on the limb with the AFO will also be scored using on an 5-point scale (1 - no pain to 5 – very severe). Pain will be recorded after each activity in the Activities Trial and after the 2-minute-walk-test (see below). During the community trial phase, pain will be assessed at the conclusion of each two-week AFO trial period. Pain will also be assessed as a screening measure (see inclusion/exclusion criteria). using the PROMIS Pain Intensity (short form 3a) and Interference subscale (short form 6b). During the community trial phase, pain intensity and interference will reflect the past seven days. The PROMIS Pain Intensity and Pain Interference subscales are universal, rather than disease specific, have high reliability, and high construct validity with related health outcomes [26].

• **Activities-Specific Balance Confidence Scale** (ABC-5 Scale). The ABC-5 Scale is a subjective measure of confidence in balance or unsteadiness when performing a variety of movements. These movements are specific to activities of daily living. It can be used to assess fall risk among cohorts of individuals with balance limitations. For example, scores of <67% indicate a risk for falling and can accurately classify individuals who fall 84% of the time [27]. This scale has been used in a wide variety of patient populations with lower limb impairments, including individuals with lower limb trauma, such as amputation [28, 29]. The ABC will be assessed at intake to characterize the participant cohort. The questions relating to walking around the house (substitute “treadmill”), walking up stairs, and walking up and down a ramp will be used for in-lab testing and the ABC will be assessed at the conclusion of the Activities Trial in each AFO condition. During the community trial phase, the full ABC will be assessed at the conclusion of each two-week AFO trial period.

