• **Quebec User Evaluation of Satisfaction with assistive Technology** (QUEST 2.0). The QUEST 2.0 evaluates a user’s satisfaction with various assistive technologies [30]. This 12-item instrument incorporates eight items to assess characteristics in terms of 1) size, 2) weight, 3) adjustments, 4) safety, 5) durability, 6) simplicity of use, 7) comfort, and 8) effectiveness. Subjects are asked to rate their satisfaction for the device on a five point scale. Four additional items related to service include 9) service delivery, 10) repairs and service of the device, 11) professionalism of service, 12) follow-up service will not be assessed as part of this study. Subjects are asked to choose the three most important items related to their assistive device. The QUEST 2.0 has been used in a variety of patient populations with lower limb injuries, including individuals with amputation [31] and in a range of orthotic applications [32]. The QUEST will be assessed at the start of the initial session to characterize the participant cohort. The QUEST will also be assessed at the conclusion of each two-week AFO trial period.

• **Orthotics and Prosthetics Users’ Survey** (OPUS). The OPUS is a self-report questionnaire consisting of five modules [33]. In the proposed work, we will be incorporating the following two modules related to the lower extremity: 1) Lower Extremity Functional Status Measure and 2) OPUS- Satisfaction with Devices and Services (questions 1-11 only). The first is based on a five-point Likert scale and nominal Yes/No scale while the second uses a six-point Likert scale. The OPUS can be used in all ages and with unilateral or bilateral prosthetic/orthotic users, congenital or acquired populations, and with all levels of orthosis and/or prosthesis use. The OPUS will be assessed at the start of the initial session to characterize the participant cohort. During the in-lab testing, the OPUS Lower Extremity Functional Status Measure questions relating to balance while standing, walking around indoors, walking up a ramp, and climbing a flight of stairs will be used. All questions will be assessed following each community trial test All questions relating to satisfaction with device (1-11) will be used after each community trial test.

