• **Orthotic Patient Reported Outcomes – Mobility** (OPRO-M). The OPRO-M is a self-report 20 item questionnaire (publications in preparation) examining the ability of the participant to complete a range of challenging everyday mobility tasks with their assistive device(s). The OPRO-M is based on a five-point Likert scale. The OPRO-M will be assessed at the start of the initial session to characterize the participant cohort and following each community trial test.

• **Self-Reported Wear Time.** The participant will be asked to record approximately how many hour the study brace/AFO was worn during each day of the take home period.

• **Feedback.** The participant will be asked to provide any feedback they may have on the study, their participation in the study, or the braces used at the conclusion of their participation in the study.

**Performance Tests**. Participants will complete a series of performance tests. These measures each relate to the questionnaire-based measures described above. For example, the Narrowing Beam Walking Test objectively measures balance while the ABC subjectively infers balance from self-report.

• **Two-Minute Walk Test** (2MWT). The 2MWT assesses walking ability. Participants will be asked to walk the greatest distance they can in 2 minutes while walking a 15.2m ‘out and back’ course until asked to stop [34]. The distance walked will be recorded as will the post-test rate of perceived exertion (Borg CR 10 scale) [35]. The 2MWT has been routinely as part of prosthetics and orthotics research. The 2MWT has been found to be valid and reliable in multiple diagnostic groups including those with lower limb amputation, neurologic impairment and others [36]. Meta-analyses and reviews report improvements in walking and mobility as a result of AFO use, so it is reasonable to expect that improvements in these areas [37-39].

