## 4.6 Data Analysis

**Aim 1.** The purpose of Aim 1 is to test the ability of the AFO emulator to reproduce the user experience of wearing actual AFOs during different activities (walking, running, stair climbing; level ground, ramps) in individuals with lower limb musculoskeletal injury. We will consider the outcome measures as continuous response variables in the statistical analysis. We will evaluate the data from the in-lab actual and in-lab *emulated* sessions using a linear mixed effect (LME) regression with the *emulated* AFO data as the independent fixed effect, the *actual* AFO data as the dependent fixed effect, and subject participant as a random intercept.

**Hypothesis 1A**. In Specific Aim 1A, we are testing the hypothesis that the experimental AFO preference measured during the in-lab *emulated* session will be significantly correlated with the experimental AFO preference measured during the in-lab *actual* session. This model estimates a change in *actual* AFO preference per unit change of *emulated* AFO preference.

**Hypothesis 1B**. In Specific Aim 1B, we are testing the hypothesis that self-reported measures and biomechanics will be significantly correlated between the in-lab *emulated* session and the in-lab *actual* session. This model operates the same as in 1A, substituting measures of function and mobility for preference.

**Aim 2.** The goal of Aim 2 is to determine if the in-lab (*emulated* and *actual*) measurements are a good predictor of the longer-term measurements made following a take home trial. To perform this analysis, we compute a similar LME regression as Aim 1 with the *emulated* *or actual* in-lab AFO data as the independent fixed effect, the *actual* take-home trial AFO data as the dependent fixed effect and subject participant as a random intercept.

**Hypothesis 2A**. In Specific Aim 2A, we are testing the hypothesis that the experimental AFO preference measured during the in-lab *emulated* session will be significantly correlated with the experimental AFO preference measured during the take home-trials. This model operates the same as in 1A, substituting measures of take-home trial preference as the dependent variable.

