**Hypothesis 2B**. In Specific Aim 2B, we are testing the hypothesis that the experimental AFO preference measured during the in-lab *actual* AFO session will be significantly correlated with the experimental AFO preference measured during the take home-trials. This model operates the same as in 1A, substituting measures of take-home trial preference as the dependent variable.

**Hypothesis 2C**. In Specific Aim 2C, we are testing the hypothesis that measures of preference will be significantly correlated between the *emulated* in-lab session and measures of performance and self-reported measures of mobility at the take-home trials. This model operates the same as in 2A, substituting measures of performance and self-reported outcomes for preference as the dependent variable.

**Hypothesis 2D**. In Specific Aim 2D, we are testing the hypothesis that measures of preference will be significantly correlated between the *actual* in-lab session and measures of performance and self-reported measures of mobility at the take-home trials. This model operates the same as in 2A, substituting measures of performance and self-reported outcomes for preference as the dependent variable.

**Power Analysis for Aims 1 & 2**. Our power analysis is based upon pilot data collected for a similar study using prosthetic feet which tested mobility and preference for three participants and two feet between *emulated* and *actual* sessions. Based upon the estimates of slope and residual error from the pilot data, 10,000 datasets were created for a sample size of N=50. Power, estimated as the proportion of datasets that rejected the null hypothesis of a slope equal to zero, was 97% for the preference scores and 98% for the mobility scores. To account for a 12% dropout rate (note that prior prosthetic emulator study experienced a 7% dropout rate) a total sample of N=56 participants will be tested.

**Exploratory Aim**. In this exploration, participants will be allowed to dynamically “dial-in” and change in the stiffness settings of the emulator device so that they design an optimal device to meet their needs. The *emulated* device will then be compared to the device that was clinically prescribed for them as part of usual care. To test the hypothesis a simple paired t-test will be used which compares the preference means and other outcomes measures of the patient-optimized and clinician-optimized conditions.

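### The 2C and 2D slopes blend differences between AFOs with differences between people, so a significant result need not mean that preferring an AFO predicts doing better in it

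*Protocol*

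**What the plan says.** Section 4.6 (Data Analysis) states the Aim 2 goal as finding out whether in-lab measurements "are a good predictor of the longer-term measurements made following a take home trial". The model is given term by term: the emulated or actual "in-lab AFO data as the independent fixed effect", and the "take-home trial AFO data as the dependent fixed effect and subject participant as a random intercept". For both 2C and 2D the protocol adds: "This model operates the same as in 2A, substituting measures of performance and self-reported outcomes for preference as the dependent variable". In-lab preference is thus the only named predictor. It is not centred, and no earlier measurement of the outcome enters.

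Such measurements are collected. Section 4.5 has three of the mobility and function questionnaires taken at entry:
- ABC: "The ABC will be assessed at intake to characterize the participant cohort".
- OPUS: "The OPUS will be assessed at the start of the initial session to characterize the participant cohort".
- OPRO-M: "The OPRO-M will be assessed at the start of the initial session to characterize the participant cohort and following each community trial test".

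The performance tests (2MWT, FSST, NBWT, shuttle run) are done in the in-lab actual-AFO session, before the community trials. They are not listed at intake and are not done on the emulator.

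The Objectives word question 2c as one of correlation: "Do measures of user preferences identified during a brief test-drive session correlate with performance measures and self-reported measures of mobility after the same" AFO has been worn in the community. Question 2d is worded in the same way.

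**The concern.** In 2C and 2D the predictor (liking a device) and the outcome (distance walked, balance, mobility score) are different constructs. Both can vary with a participant's general ability. The protocol recruits across mobility levels and expects some participants not to run, so stable differences in ability are likely.

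A random intercept absorbs part of those differences but does not adjust for them. It treats the participant effect as unrelated to preference, and the one slope becomes a weighted average of the within-person and between-person slopes. If fitter people rate every AFO higher, the slope is positive even when no one does better in the AFO they prefer.

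What is at stake is the use of the result. The test-drive strategy is meant to help choose among devices for one patient, and only the within-person part of the association bears on that choice.

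**Working it through.** **The plan's own figures.** Section 4.6 gives 97% and 98% power at N=50 for a test of slope zero. Slope, residual error, participant variance and alpha are not stated, so these cannot be reproduced. At an assumed two-sided 0.05 they imply slope/SE of about 3.84 and 4.01. They come from a pilot comparing emulated with actual sessions, and so say nothing about the blend examined here.

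**Inputs.** From the protocol: 50 analysed participants, 3 AFOs, random intercept, test of slope zero. Assumed: alpha 0.05 two-sided; outcome ICC 0.7; preference ICC 0.3, 0.5 or 0.7; both variables with variance 1; correlation r between ability and a person's general liking of 0, 0.3 or 0.5; true within-person slope zero.

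**Hand check, preference ICC 0.5, r = 0.5.**
- Down-weighting of between-person information: 1 + 3 × 0.7/0.3 = 8.
- Variance of a participant's mean preference: 0.5 + 0.5/3 = 0.667.
- Between-person information per participant: 3 × 0.667/8 = 0.25. Within-person: 2 × 0.5 = 1.0.
- Between-person share of the slope: 0.25/1.25 = 0.20.
- Between-person slope: 0.5 × √(0.7 × 0.5)/0.667 = 0.444.
- Expected planned slope: 0.20 × 0.444 + 0.80 × 0 = 0.089.
- SE: √(0.3/(50 × 1.25)) = 0.069, so slope/SE = 1.28 and the rejection probability is about 25%.

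Simulation gives a mean slope of 0.095 and 28% rejection, close to this approximation.

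**Simulation.** 1,500 datasets per row, REML random-intercept model, outcome ICC 0.7. The baseline has reliability 0.8, that is, a correlation of √0.8 = 0.89 with ability.

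| r | Preference ICC | Planned model | Plus baseline | Deviation term after split |
|---|---|---|---|---|
| 0 | 0.5 | 5.5% | 6.2% | 5.3% |
| 0.3 | 0.3 | 9.7% | 7.5% | 6.7% |
| 0.3 | 0.5 | 13.9% | 9.0% | 5.8% |
| 0.3 | 0.7 | 22.5% | 8.5% | 5.1% |
| 0.5 | 0.3 | 15.5% | 8.2% | 5.5% |
| 0.5 | 0.5 | 27.8% | 13.0% | 5.5% |
| 0.5 | 0.7 | 49.6% | 16.5% | 5.7% |

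A separate simulation on the same grid gave 9–23% (r = 0.3) and 16–54% (r = 0.5) for the planned model. With a weaker baseline, correlating 0.8 with ability, it gave 7–13% and 12–27%. The split gave about 5–7%, and every model about 5–6% at r = 0.

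**Wider range.** Over outcome ICC 0.5–0.9, preference ICC 0.3–0.7 and r 0.3–0.7, the planned model rejects in 6–90%. The effect is small (6–12%) when outcome ICC is 0.9 and preference ICC 0.3.

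**Precision.** With r = 0 and a common slope of 0.12 within and between people, power is 43% for the planned model, 51–62% with the covariate (baseline correlation 0.8 to 0.95), and 37% with the split alone. This ordering depends on the slope being common. When the association was placed only within persons (0.2 in within-person SD units), power was 50.5% as planned, 45.2% with the covariate and 54.4% with the split.

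**The case against.** The strongest reply is that 2C and 2D ask only whether preference correlates with later outcomes. If able people like AFOs more, that correlation exists, and rejecting slope zero answers the question as written. This stands. A reader might infer from the table that the planned test has an inflated false-positive rate. The documents do not support that, because the rates are errors only against an AFO-specific null that 2C and 2D do not state. What remains is the step from the crude slope to the prediction that Aim 2 sets as its goal.

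Second, nothing in the protocol shows that ability and liking are correlated, or how stable preference ratings are within a person. This also stands: the size is conditional, and at r = 0 there is no distortion.

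Third, a reader might infer that baseline adjustment alone cures the problem and leaves the question unchanged. It does neither. Baseline scores carry error, so some of the blend remains (12–27% at r = 0.5 with a baseline correlating 0.8 with ability), and the adjusted slope estimates something other than the crude correlation.

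Fourth, covariates are often left to a SAP, which is not shown here and may add them. But the protocol itself names the fixed and random terms, so the point concerns what it fixes. Preference is the primary outcome, and 2A and 2B lie outside this point.

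**Conclusion.** The concern holds in a limited form. As specified, the 2C and 2D slope is a legitimate crude association, but it cannot separate liking a particular AFO from being a more able person who likes AFOs. If ability and liking correlate at 0.3 to 0.5, the planned test would be significant in roughly 9–54% of datasets with no AFO-specific link, given outcome ICC 0.7 and preference ICC 0.3 to 0.7. All of these inputs are assumptions. With no such correlation the rate is about 5–6%.

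This does not invalidate the hypotheses as worded. It limits the conclusion they can carry and is worth correcting before analysis, since the data needed are already collected.

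**What to change.** 1. In 2C and 2D, add one participant-level covariate: the intake score of the same instrument for ABC, OPUS and OPRO-M; for 2MWT, FSST, NBWT and shuttle run, the participant's mean in-lab result over the three actual AFOs.
2. Also fit each model with preference split into the participant's mean and the deviation from it. Report both coefficients, and base any AFO-specific conclusion on the deviation term. With complete data the covariate in step 1 does not alter that term, because a participant-level covariate is orthogonal to within-person deviations. The two steps serve different purposes.
3. State that the unadjusted slope, if still reported, is a crude correlation.

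Cost: one covariate and one extra fit per model, with no new visits or instruments. Downsides: the adjusted slope is no longer the crude correlation. The in-lab performance mean is not a pre-exposure baseline; for 2D it comes from the same session as the preference score. Missing intake scores need a simple rule. The split alone has somewhat lower power if the slope is common within and between people (about 37% against 43% at an assumed slope of 0.12).

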# Objectives

The overarching goal of this research is to optimize mobility, function and satisfaction for Service members, Veteran, and civilian AFO users with lower limb musculoskeletal injuries. To achieve this, our primary purpose is to determine the extent to which a ‘test-drive’ strategy, using an AFO emulator, can be used to predict device function, mobility and preference outcomes with corresponding commercially available (*actual*) AFOs in Service members and Veterans with lower limb musculoskeletal trauma.

**Specific Aim 1**: Test the ability of the AFO emulator to reproduce the user experience of wearing *actual* AFOs during different in-lab activities (walking, running, stair climbing; level ground, ramps) in individuals with lower limb musculoskeletal injury. This aim will determine if the proposed AFO emulator framework can provide an option for quickly exploring multiple devices in a short period of time.

**Research Question 1a**: Do self-reported measures of preference differ between *emulated* and corresponding *actual* AFO conditions?

**Hypothesis 1a**: Preference scores for *emulated* AFO conditions will be strongly correlated with preference for the corresponding *actual* AFO.

**Research Question 1b**: Do measures of performance and self-reported outcomes differ between *emulated* and *actual* AFOs conditions?

**Hypothesis 1b**: Measures of performance and self-reported outcomes in the *emulated* AFO condition will be strongly correlated with those using corresponding *actual* AFOs.

**Specific Aim 2*:*** Test the ability of a short-term, in-laboratory evaluation of function, mobility, and preference to predict those same outcomes longer-term (i.e., after 2 week use in the community) in AFO users with lower limb musculoskeletal injury. This aim will determine the predictive ability of a brief test-drive strategy using *actual* and *emulated* AFOs to identify function, mobility, satisfaction, and preference at follow-up after two weeks of use in the community environment with corresponding *actual* AFOs.

**Research Question 2a**: Do measures of user preferences identified during a brief test-drive session with an *emulated* AFO predict user preferences after the *actual* AFO is worn longer-term in the community environment?

**Hypothesis 2a**: Initial preference scores for each *emulated* AFO will be strongly correlated with preference for the corresponding *actual* AFO at follow-up.

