• **Four-Square-Step-Test** (FSST). The FSST is a test of balance and agility [40] where the patient must change directions quickly while maintaining balance. A 1-inch high obstacle in the shape of a Maltese cross is placed on the floor. The participant is instructed to begin in the back, left quadrant then to move 1) forward, 2) sideways right, 3) backward, then 4) sideways left, then to move in the reverse direction back to the original square. They move as fast as possible through their movement progression while keeping one foot on the floor at all times. The only materials required are pieces of PVC pipe and a stop watch. Participants will complete one practice and two successful trials. In healthy, active duty Service members, inter-rater reliability was excellent (ICC = 0.99, 95% CI = 0.99-0.99) and test-retest reliability was good (ICC = 0.86, 95% CI = 0.75-0.96) [41]. In individuals with amputations, the Four-Square-Step-Test has high sensitivity (92%), specificity (93%) and predictive values (positive: 86%; negative: 96%) for identifying fall risk.

• **Narrowing Beam Walking Test** (NBWT). The NBWT is a reliable and valid task that challenges balance abilities in healthy and impaired populations [42, 43]. Participants walk with arms crossed along a 6.71m beam of narrowing width until they can no longer maintain balance and step off the beam. The distance of the last foot position on the beam is recorded. Five trials can accurately estimate usual balance performance in groups such as lower limb prosthesis users [43]. The NBWT demonstrates strong correlations (0.70-0.85) with performance on other balance tasks such as TUG, FSST, and Berg Balance Scale and moderate correlations (0.49) with the ABC Scale. Performance is significantly lower among individuals of lower mobility levels. There are no floor or ceiling effects indicating that the NBWT measures broad ranging balance abilities without reaching scale limits [42].

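### Hypotheses 1a, 1b and 2a-2d claim a strong correlation, but section 4.6 tests and powers only for a non-zero slope, which cannot establish strength

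*Protocol*

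**What the plan says.** **Objectives.** Each Aim 1 and Aim 2 hypothesis is a claim about strength:

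- 1a, preference for the emulated devices: "AFO conditions will be strongly correlated with preference for the corresponding" actual AFO.
- 1b, performance and self-reported outcomes: "AFO condition will be strongly correlated with those using corresponding" actual AFOs.
- 2a, emulated in-lab preference against follow-up: "AFO will be strongly correlated with preference for the corresponding" actual AFO.
- 2b, actual in-lab preference against follow-up: "AFO be strongly correlated with preference at follow-up".
- 2c and 2d, emulated and actual in-lab preference respectively: "preference scores be strongly correlated with performance-based and self-reported mobility measures at follow-up".

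**Section 4.6 Data Analysis.** The same six hypotheses are restated with a different adverb. For 1A, emulated preference "will be significantly correlated with the experimental AFO preference measured during the in-lab" actual session, and the others follow the same pattern. The tool is a linear mixed model with a random participant intercept, with the emulated (or in-lab) score as predictor and the actual (or take-home) score as response. The power paragraph makes the null explicit: "Power, estimated as the proportion of datasets that rejected the null hypothesis of a slope equal to zero, was 97% for the preference scores". It gives 98% for mobility, at N = 50, raised to 56 for dropout.

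**Section 4.5 Study Evaluations.** Preference is named as the primary outcome. In describing the beam-walking test, this section also shows how the document uses the word elsewhere: "The NBWT demonstrates strong correlations (0.70-0.85) with performance on other balance tasks", with 0.49 against the balance-confidence scale called moderate.

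**The concern.** A test of slope = 0 asks whether there is any linear association. It does not ask how strong the association is, and a slope in rating points also depends on how widely the predictor ratings spread. Following section 4.6 as written, a small p-value would be read against hypotheses that claim much more.

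This touches the primary outcome and the purpose of the trial. Aim 1 asks whether the emulator reproduces what it is like to wear the real device, and Aim 2 whether a short session predicts preference after two weeks at home. The same person rates what is meant to be the same device twice, so some association is to be expected and rejecting zero is a low bar. If the meaning of *strong* is settled only once the data are in, the main conclusion is open to choice after the fact.

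**Working it through.** **1. The plan's own figure.** The 97% and 98% cannot be reproduced. The pilot slope, the residual error, the spread of the predictor, alpha and the simulated data layout are not given. The working below takes the plan's N = 50 and three AFOs per participant (sections 4.5 and 4.6) and assumes two-sided alpha = 0.05.

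**2. Smallest observed correlation that reaches significance.** r = t / √(t² + df), with t the 97.5% point. The degrees of freedom are 50 − 2 = 48 for one pair per participant, 150 − 50 − 1 = 99 within participants, and 150 − 2 = 148 if all pairs are treated as independent.

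**3. Chance of significance at a given true correlation.** Fisher z: Φ(√(m − 3) · atanh r − 1.96), with m = df + 2.

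| Layout at N = 50 | df | Smallest significant observed r | Power, true r = 0.20 | Power, true r = 0.30 |
|---|---|---|---|---|
| One pair each | 48 | 2.011/√(4.04 + 48) = 0.28 | 28% | 56% |
| Three AFOs, within participant | 99 | 1.984/√(3.94 + 99) = 0.196 | 52% | 87% |
| Three AFOs, 150 pairs as independent | 148 | 1.976/√(3.90 + 148) = 0.16 | 69% | 96% |

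With all 56 participants and three AFOs each, the thresholds fall slightly, to 0.185 (within) and 0.15 (independent pairs).

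**4. Check against the planned model.** A random-intercept model was simulated for 50 participants × 3 devices. It used 1,000 datasets per setting, intraclass correlations of 0, 0.3 and 0.5, and the same correlation between and within participants. It rejected slope = 0 in 68-69% of datasets at a true r of 0.20 and in about 96% at 0.30. Datasets with p near 0.05 had a pooled correlation of about 0.15 to 0.18.

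**5. Can the planned effect be recovered?** No. Solving 97% power for r with r = tanh((1.96 + 1.88)/√(m − 3)) gives:

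- 0.51 for one pair each;
- 0.37 within participants with three AFOs;
- 0.31 for 150 independent pairs;
- about 0.14 if five activity ratings per AFO were analysed within participants (df = 750 − 50 − 1 = 699).

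The answer depends on a layout that the protocol does not report.

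**6. What a criterion for strength would cost.** For a within-participant correlation, m = 101 and the standard error on the z scale is 1/√98 = 0.101.

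- Lower 95% limit above 0.50: the observed r must be about tanh(0.549 + 1.96 × 0.101) = 0.63. Power at a true r of 0.70 is Φ((0.867 − 0.549)/0.101 − 1.96) = Φ(1.19), about 88%.
- Lower 95% limit above 0.70: the observed r must be about 0.79. Power at a true r of 0.80 is Φ((1.099 − 0.867)/0.101 − 1.96) = Φ(0.33), about 63%.

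**The case against.** Several arguments can be made for the plan, and some of them stand.

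- *No formal success rule is written.* The zero-slope null appears only in the power paragraph, and section 4.6 also promises an estimate of how far the actual rating moves per point of the emulated rating. A weak slope would therefore be visible, and grading it could be left to a SAP. This is fair as far as a missing threshold goes. It does not remove the conflict between two things the protocol itself states: strong in the Objectives, significant in 4.6.
- *The cut-off of 0.20 is not exact for this model.* This stands. The predictor is not centred within participants, so the planned slope mixes within- and between-person association. The simulation places the boundary in the same region.
- *The 0.70-0.85 range is not a threshold for this trial.* This stands. It describes published correlations of the beam test with other balance tests. It shows only how the document uses the word.

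A reader might also infer more than the documents support:

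- That every hypothesis is affected. Exploratory hypothesis 3a is a difference in means with a paired t-test.
- That a correlation near 0.2 would confirm all six. The 0.16 to 0.20 is an observed value for one test. A true r of 0.20 would be significant in roughly 52% to 69% of trials with three AFOs each. The 4% of variance that 0.20² implies is a boundary case, not an expected result.
- That the trial was planned around a weak correlation. Step 5 of the working shows that the planned effect cannot be recovered.
- That the power is miscalculated. Nothing in the document shows this.

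**Conclusion.** The mismatch is real and concerns the primary outcome. Six hypotheses claim strength, while the analysis and its power address only the existence of an association. Under two-sided 0.05 and N = 50, significance needs an observed correlation of only about 0.16 to 0.20 with three AFOs per participant, or 0.28 with one pair each. These values are far below what the protocol calls strong for another instrument. A significant slope would thus not support the hypotheses as stated, nor a conclusion that the emulator reproduces AFO preference or predicts it well.

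The figures rest on an assumed alpha and on how pairs are counted. The conclusion does not, because a zero-slope test cannot establish strength under any layout. The 97% and 98% may be correct for what they measure. They say nothing about the chance of showing a strong correlation.

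**What to change.** Reconcile the Objectives with section 4.6 in one of two ways.

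1. **Keep the claim of strength.** For hypotheses 1a, 2a and 2b, report the within-participant (repeated-measures) correlation with a 95% CI alongside the mixed-model slope. Conclude that scores are strongly correlated only if the lower limit exceeds a threshold that the sponsor fixes before the data are seen. Restate power for that criterion. As illustrations, it is about 88% for a lower limit above 0.50 if the true r is 0.70, and about 63% for a lower limit above 0.70 if the true r is 0.80. The threshold is the sponsor's choice. Give 1b, 2c and 2d the same kind of rule, or remove *strongly* from them.
2. **Keep the zero-slope test.** Delete *strongly* from hypotheses 1a to 2d and limit the conclusion to association.

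Both are changes of wording and reporting. Neither alters visits, data collection or the fitted model, and neither in itself calls for more participants. The first route costs a less favourable power statement, and more so the stricter the threshold. The second costs a more modest conclusion.
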